### Intervention

The intervention will be introduced to the mother following allocation into the massage group. The massage paradigm is modified from the preterm massage protocol of Field et al. [89] that consists of 2 parts, a tactile phase and a kinaesthetic phase. Mothers will be taught the techniques and encouraged to massage their babies for 15 min, twice a day until term equivalent age. Those allocated to the control group will receive care as usual.

Mothers will be given the following instructions both in demonstration and in written form for later reference. The tactile phase will begin with asking “baby’s permission”, in the prone position and enclosing the infant with cupped hands in a “resting hands” position (Fig. 1). A small amount of massage oil (cold-pressed fruit or vegetable oil) will be used. Maintaining a “resting hand” to the back, the mother will slowly stroke the baby with the palm of her other hand with a gentle but firm, rhythmic motion, following this sequence: head to the neck (6 times), shoulder to the hand (6 times) left and right, neck to the back to the bottom (6 times), bottom to the feet (6 times) left and right. After returning to “resting hands” position for up to a minute, this sequence will be repeated. During the massage the mother is to breathe deeply and slowly, keeping herself relaxed whilst paying attention to the baby’s stress cues which include crying, skin mottling, hiccups, gagging, apnoea and bradycardia. If signs of stress are evident, the mother will to return to “resting hands” until the baby settles and is ready for further massage. If the baby doesn’t settle, the mother will stop and re-attempt the massage later.

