**Fig. 1 Fig1:**
[figure not shown]
"Resting hands" prone position in massage protocol

For the kinaesthetic phase, the baby is placed in the supine position. Again, the mother will place her palms on the baby’s body to embrace the chest in a “resting hands” position. If the baby’s eyes are open, eye contact and verbal interaction will be encouraged. Kinaesthetic stimulation will follow this sequence: 6 flexions and extensions of the right upper limb, 6 flexions and extensions of the left upper limb, 6 flexions and extensions of the right and left upper limbs together, 6 flexions and extensions of the right lower limb, 6 flexions and extensions of the left lower limb, 6 flexions and extensions of the right and left lower limbs together. After returning to “resting hands” position for up to a minute, this concludes the session. The massage sequence will be taught to the mother by the same paediatric physiotherapist trained in the Field method of massage [89].

The mothers will be provided with a structured diary to keep a record of the number and duration of each session. Massage sessions will be preferably performed around 60 min before feeding and at least 2 h after the completion of the previous session. Up to three individual teaching sessions will be given to each mother and support will be continued until the mother is considered to be competent and confident. Regular contact with the mother will ensure that she continues to use the outlined protocol. When the baby is discharged home, the mother will be asked to continue daily massages until TEA.

Infants of the CAU group will undergo routine nursery care and there will be no specific interventions. Intervention and CAU mothers will be assigned to different nursery rooms to prevent contamination. In addition, nursery staff will be briefed on the importance of maintaining the study protocol. Very close monitoring of the data collection process will ensure protocol violations will be identified and action will be undertaken to prevent this, in a sensitive manner.

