### Data analysis

Summary statistics will be used to describe demographic and clinical data characteristics at baseline by allocated study treatment. Continuous data will be summarised using either mean and standard deviation, or median and inter-quartile range, depending on the distribution of the variable of interest. Categorical data will be presented as frequencies and percentages. Comparisons between the baseline values of the treatment groups will be conducted to assess the degree to which variables are comparable after randomisation. Between group differences will be investigated using linear regression for continuous data and Fisher’s exact test for categorical data. Potential confounding variables for the primary outcome are considered a-priori to be: gestational age at birth, birthweight, parity and maternal education. If any of these variables differ significantly between-groups (at *P* < 0.005), the identified variable(s) will be controlled for in the main analyses.

The primary study outcome is beta frequency global power measured in all VPT infants at term equivalent age. The mean difference between treatment groups will be calculated using linear regression with treatment group entered as the main effect. The corresponding 95 % Wald confidence interval and *p*-value will be reported. For secondary outcomes, we will present the effect estimate relating to a variable with a continuous outcome as a mean difference, which will be calculated using a linear regression model. If a continuous variable does not meet the assumptions necessary for linear regression, we will compare groups using the Mann–Whitney U Test. We will present the effect estimate relating to a variable with a binary outcome as an odds ratio, which will be calculated using a logistic regression model. We will present the effect estimate relating to a variable with a count outcome as an incident rate ratio, which will be calculated using a Poisson regression model. For all models the corresponding 95 % Wald confidence interval and p-value will be reported.

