All analyses will primarily be undertaken using the ‘intention-to-treat’ approach, where all evaluable data is analysed in the treatment group according to which the participant was allocated, regardless of treatment received. Additionally, ‘per protocol’ analyses will be conducted where there have been large deviations from the planned intervention; all individuals with evaluable outcome data will be analysed according to the treatment they received (no massage/received < 50 % of total possible massage/received at least 50 % of total possible massage). Any such analyses will be clearly labeled as such and cautiously interpreted as perhaps indicating the maximum theoretical potential of the intervention. Statistical significance will be defined as alpha = 0.05. All tests conducted will be two-tailed.

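### The supplementary analysis called per protocol is an as-treated comparison, and its hedged reading as the intervention's maximum potential is unsupported

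*Protocol article*

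**What the plan says.** All of this is in the protocol article.

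- **Primary approach** (Data analysis): "All analyses will primarily be undertaken using the ‘intention-to-treat’ approach".
- **Supplementary analysis** (same section): where deviations from the planned intervention are large, an additional analysis named per protocol is run. In it "all individuals with evaluable outcome data will be analysed according to the treatment they received". The groups are "no massage/received < 50 % of total possible massage/received at least 50 % of total possible massage".
- **Planned reading:** the result is to be flagged under that name and "cautiously interpreted as perhaps indicating the maximum theoretical potential of the intervention".
- **Confounders:** four are named in advance (gestational age, birthweight, parity, maternal education). If any differs between groups at P < 0.005, "the identified variable(s) will be controlled for in the main analyses". Nothing is said about adjusting the comparison by massage received.
- **Dose** (Intervention): mothers are "encouraged to massage their babies for 15 min, twice a day until term equivalent age". On signs of stress the mother goes back to a resting hold; if the infant does not settle, she stops and tries again later. After discharge, "the mother will be asked to continue daily massages until TEA".

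**The concern.** A per-protocol analysis normally stays within the allocated arms and leaves out participants who departed from the protocol. Here nobody is left out and the arms are dissolved. Controls and randomised mothers who never massaged fall into one category, and the massage arm is spread over three. The groups compared are therefore no longer those that randomisation made alike.

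The amount of massage is not assigned at random within the massage arm. It depends partly on whether the infant tolerates it, and the mother delivers it, so it plausibly also depends on her mood and engagement. Infants in the top category may differ from the rest in ways that matter to EEG power, and maternal mood and attachment are themselves secondary outcomes. The four named confounders cover neither stability after birth nor maternal mood.

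At stake is what the trial may say if the primary result is null or weak. An apparent gradient by dose could come from selection alone, and the article offers a reading of it, as the most the intervention could achieve, that the comparison cannot bear.

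**Working it through.** **What the analysis is.** Three features settle it: the population is everyone with outcome data, the grouping variable is massage received, and allocation plays no part. That is an as-treated comparison. Flagging the result under its planned name would attach the wrong name to it.

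**The design's own figures.** Sample size: 20 completers per group and two thirds retained gives 20 / (2/3) = 30 per group, 60 in all, as stated; about 40 infants are expected to be evaluable. No SD is given for the 10% difference. Back-solving 80% power at two-sided 0.05 with 20 per group gives (1.960 + 0.842) × √(2/20) = 0.886 SD (normal approximation) or 0.909 SD (t-test). The t-test value implies an SD of 10 / 0.909 = 11.0% of the mean. It serves only as a yardstick.

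**Illustration of selection bias with no true effect.** Assumed, not from the document: 60% of massage mothers reach at least half, and adherence correlates r with the outcome.

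- Top category minus controls: r × φ(z) / p, with p = 0.6, z = −0.253, φ(z) = 0.386. The factor is 0.386 / 0.6 = 0.644.
- Top category minus the rest of the massage arm: r × (0.386/0.6 + 0.386/0.4) = r × 1.610.

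| r | vs controls (SD) | vs rest of massage arm (SD) |
|---|---|---|
| 0 | 0 | 0 |
| 0.2 | 0.13 | 0.32 |
| 0.3 | 0.19 | 0.48 |
| 0.5 | 0.32 | 0.80 |

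Against the back-solved 0.909 SD, the 0.13 to 0.32 SD is about 14% to 35% of the design effect. A negative r gives the same sizes with the sign reversed, so the contrast is not an upper bound.

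**Null simulation.** The first column above leaves out massage-arm mothers who never massaged and are pooled with controls. A simulation includes them: 20 evaluable infants per arm, SD 11% of the mean, 10–20% of the massage arm with none and 30% under half, 0–20% of controls crossing over, 4,000 runs per setting. The contrast is at least half versus none.

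| r | Spurious difference (points; design target 10) | Type I error |
|---|---|---|
| 0 | about 0 | 5.1–5.4% |
| 0.2 | 1.7–3.0 | 6–11% |
| 0.3 | 2.6–4.4 | 9–18% |
| 0.5 | 4.4–7.4 | 18–41% |

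Intention-to-treat on the same data showed a mean difference near 0 and type I error of 4.4–5.8% throughout.

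**The 50% cut.** One sentence gives twice a day up to term equivalent age; another says daily after discharge. Suppose massage starts at 33 weeks, discharge is at 36 and term equivalent age is taken as 40 (all assumed): 21 days in hospital and 28 at home. Twice a day throughout gives 2 × (21 + 28) = 98 sessions. If daily means once a day after discharge, the total is 2 × 21 + 28 = 70. A mother with 40 sessions is at 40/98 = 41% or 40/70 = 57%, on opposite sides of the cut.

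**The case against.** The strongest reply is that the article already hedges. Intention-to-treat is primary, the analysis by massage received is additional and conditional, and its reading is qualified by cautiously, perhaps and theoretical. This stands. A reader might infer that a confounded contrast will be presented as efficacy, or that the trial's main conclusion is at risk; the text supports neither. The hedges do not rescue the reading itself, though, because caution about an upper bound does not make the contrast one.

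Other stronger readings also fail or are weakened:

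- **Massage simply ends when an infant shows stress.** The Intervention section has the session paused, and stopped only if the infant does not settle, with another attempt later. Infants must also be clinically stable and off respiratory support at entry. The link between tolerance and dose is weaker than outright stopping would make it, but not absent.
- **The trigger is judged on outcome data.** The article does not say so. Deviations can be read from diaries alone, EEG and MRI analyses are blinded, and a threshold for large may sit in the unseen analysis plan.
- **Controls cannot be classified.** The diary is described only for massage mothers, but the article also describes separate rooms and close monitoring for violations. Control-arm recording may be in the full protocol.
- **The two frequency statements contradict each other.** Daily may mean every day at the same frequency. The 98-versus-70 gap needs the once-a-day reading and the assumed dates. It is an ambiguity in the denominator, not a proven contradiction.
- **The bias sizes are hypothetical.** They are: no passage gives an adherence rate or a correlation.

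**Conclusion.** The point holds in limited form. The supplementary analysis is as-treated under a per-protocol name, with no stated adjustment and a dose that depends partly on infant and mother. Its reading as perhaps the intervention's maximum potential has no basis, because selection can move the contrast up or down.

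The size is not known. A spurious 0.13 to 0.32 SD against controls rests on 60% adherence and correlations of 0.2 to 0.5, all assumed; with no correlation there is no bias. The primary conclusion does not depend on any of this. Severity is should-fix: the change affects what may be said about adherence, not the main result.

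**What to change.** 1. Rename the analysis as treated, exploratory, and delete the statement about maximum potential. The three-group table can stay as description.
2. Base any adherence-adjusted claim on an estimate that keeps randomisation, such as a complier-average causal effect, or two-stage least squares with allocation as the instrument and the proportion of possible massage as the exposure.
3. State the limits of that estimate. With about 40 infants it will be imprecise: if mean exposure differed between arms by 0.6, for example, its standard error would be roughly 1/0.6 = 1.67 times that of the intention-to-treat estimate. It also assumes that allocation acts only through massage. That is doubtful for maternal outcomes, since massage mothers also receive up to three teaching sessions and regular contact. Exposure must be known in both arms; if the full protocol does not already record it for controls, it should.
4. Reconcile the two statements of massage frequency in the Intervention section, so that total possible massage has one denominator. Which schedule is meant is for the investigators to say.

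The cost is wording in the analysis plan, one clarification of the schedule and, if not already planned, brief exposure recording for controls. The primary analysis and sample size do not change.

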## Discussion

This protocol paper outlines a randomised controlled trial of infant massage in VPT infants to detect effects on neurodevelopment. To our knowledge this study is the first to directly measure what influences infant massage may have on preterm brain structure and function using EEG, MRI and neurobehavioural assessments, and the mother-infant relationship in a preterm cohort.

## Abbreviations

AFD: Apparent fibre density
Bayley-III: Bayley Scales of Infant and Toddler Development, Third Edition
BDI: Beck Depression Inventory
BSID-II: Bayley Scales of Infant Development, Second Edition
DASS: Depression Anxiety Stress Scale
dEEG: Dense array electroencephalography
DWI: Diffusion weighted imaging
EEG: Electroencephalography
EPDS: Edinburgh Postnatal Depression Scale
FA: Fractional anisotropy
FOD: Fibre orientation distribution
GMA: General Movements Assessment
HARDI: High angular resolution diffusion imaging
HNNE: Hammersmith Neonatal Neurological Examination
HREC: Human research ethics committee
ITSEA: Infant Toddler Social and Emotional Assessment
MD: Mean diffusivity
MDI: Mental Developmental Index
MIBS: Mother-to-Infant Bonding Scale
MIRI: Maternal Infant Responsiveness Instrument
MPAS: Maternal Postnatal Attachment Scale
MRI: Magnetic Resonance Imaging
MSES: Maternal Self-Efficacy Scale
NVS: Neonatal Vision Scale
PDSS: Postpartum Depression Screening Scale
PMA: Postmenstrual age
PPD: Postpartum depression
SPSS: Statistical Package for the Social Sciences
TEA: Term equivalent age
TSE: Turbo spin echo
VPT: Very preterm infant
